#### Sample size.

Sample size calculations were based on detecting changes in gait speed using a within-subject design. Assuming a standardised response mean (SRM) of 0.5 (moderate effect size) for gait speed, a two-sided significance level (α) of 0.01, and 90% power, approximately 54 participants would be required to detect a statistically significant change in gait speed for a single comparison (e.g., cued vs. non-cued walking). When accounting for the three cueing conditions and the associated adjustment for multiple (three) comparisons, we applied a Bonferroni correction resulting in an adjusted alpha of α (0.01/3 = 0.0033). That requirement increases sample size to approx. 55 participants. However, to allow for an anticipated attrition rate of up to 10%, we plan to recruit 60 participants in total. This sample size ensures adequate power to detect moderate cueing effects on gait speed, accommodates potential dropouts, and provides balanced representation across randomisation sequences.

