If assumptions for normality are not met, a Friedman test will be used to assess within-subject differences across cueing conditions. Post-hoc Wilcoxon signed-rank tests, with Bonferroni correction, will be conducted only if the Friedman test is statistically significant. For between-subject effects (e.g., walk order), where normality assumptions are violated, the Kruskal–Wallis test will be used to assess group-level differences between walk-order groups. Interaction effects between cueing and walk order will be explored non-parametrically by conducting separate Friedman tests within each walk order group. Effect sizes for non-parametric tests will be calculated using the rank-biserial correlation coefficient, $\text{r}=\text{Z}/\sqrt{\text{N}}$, providing a measure of the magnitude of the effects observed.

For the three primary comparisons, we will control the familywise error rate using a Bonferroni adjustment. Given three cueing modalities, statistical significance (*p*) will be evaluated at a two-sided α = 0.01/3 = 0.0033. Effect sizes (i.e., SRM) and 95% confidence intervals will also be reported. Secondary and exploratory analyses (e.g., comparing cueing modalities to one another, examining washout effects, assessing stride-to-stride variability) will not be subject to multiplicity correction. For these analyses, a two-sided *p*-value of 0.05 will be considered statistically significant across all parametric and nonparametric tests.

To assess whether the first cue produced short-term residual effects, we will calculate changes in gait outcomes from baseline to each cued walk and from each cued walk to its subsequent washout walk (WO1 and WO2). For each cue exposure, a carryover score will be calculated as the difference between the change induced by the cue and the change observed during the corresponding washout period, reflecting retained cue effects. The approach enables an evaluation of carryover effects after each cued walk separately, thereby capturing any cumulative or progressive retention of cueing effects. Group differences based on initial cue type (i.e., counterbalanced sequence) will be evaluated using one-way ANOVA or the Kruskal–Wallis test, depending on normality assumptions [74–80].

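### The sample sizes of 54 and 55 do not follow from the stated inputs; at the significance level the analysis will use, power is about 72–79% per cue, not 90%

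*Protocol article*

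**What the plan says.** All the inputs are in the Sample size section of the protocol article. The calculation is for a within-subject change in gait speed, "Assuming a standardised response mean (SRM) of 0.5 (moderate effect size) for gait speed", with "a two-sided significance level (α) of 0.01, and 90% power". From these the protocol concludes that "approximately 54 participants would be required to detect a statistically significant change in gait speed for a single comparison", giving cued versus uncued walking as the example. It then divides alpha by three for the three cueing conditions, to 0.0033, and states: "That requirement increases sample size to approx. 55 participants". Finally, "to allow for an anticipated attrition rate of up to 10%, we plan to recruit 60 participants in total". The paragraph closes by claiming adequate power for moderate cueing effects on gait speed, and the Justification Summary that follows calls the results from 60 participants robust and reliable.

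The Statistical analysis section confirms the threshold. For the three primary comparisons, significance "will be evaluated at a two-sided α = 0.01/3 = 0.0033".

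**The concern.** The two printed numbers are inconsistent with each other before any software is used. With effect size and power held fixed, cutting alpha to a third has to raise the requirement noticeably, yet the text adds one participant. At least one of the two figures must therefore be wrong, and the check below shows that both are.

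This is the only sample-size justification in the article and it concerns the primary comparisons. If true power is well under 90%, a cue with a real moderate effect on gait speed has a much larger chance of missing significance than the protocol says. A reader relying on the stated 90% would then give a non-significant result for that cue more weight than it deserves.

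**Working it through.** **Inputs**

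- SRM 0.5, two-sided alpha 0.01, power 90%, within-subject comparison (Sample size).
- Alpha 0.01/3 = 0.0033 for three comparisons (Sample size), confirmed as two-sided in Statistical analysis.
- 60 recruited, up to 10% attrition (Sample size).
- Assumption: the cue-versus-baseline test is a paired (one-sample) test on change scores. The protocol does not name the test for this comparison, but an SRM in a within-subject design implies it.

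**Attempt to reproduce 54 and 55**

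Normal approximation: n = ((z₁₋α/₂ + z_power) / SRM)².

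- Alpha 0.01: ((2.576 + 1.282) / 0.5)² = 59.5, so 60.
- Alpha 0.0033: ((2.935 + 1.282) / 0.5)² = 71.1, so 72.

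Exact paired t-test: the smallest n with power of at least 90%, from the noncentral t distribution with n − 1 degrees of freedom and noncentrality 0.5√n.

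- Alpha 0.01: n = 63.
- Alpha 0.0033: n = 76.

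| Two-sided alpha | Protocol | Normal approximation | Paired t |
|---|---|---|---|
| 0.01 | 54 | 60 | 63 |
| 0.0033 | 55 | 72 | 76 |

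Neither printed figure is reproduced. The step from the first alpha to the second is 72 − 60 = 12 or 76 − 63 = 13 participants, an increase of about 20%.

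Some inputs that the protocol does not state do land nearby. Two-sided 0.05/3 = 0.0167 with 90% power gives 54.04 by the normal approximation (57 by paired t), and one-sided 0.01 with 90% power gives 53 (normal) or 55 (t). These are only possible origins; the documents do not settle which, if any, was used.

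**Power actually available at two-sided 0.0033, SRM 0.5**

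Completers after 10% attrition: 60 × 0.9 = 54. By the normal approximation, power with 54 is Φ(0.5√54 − 2.935) = Φ(3.674 − 2.935) = Φ(0.739) = 77%.

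| Analysed | Paired t | Normal approximation |
|---|---|---|
| 54 | 72.2% | 77.0% |
| 55 | 73.4% | 78.0% |
| 60 | 78.7% | 82.6% |

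With 54 completers, the SRM detectable with 90% power by paired t is 0.60. Without the Bonferroni step, at two-sided 0.01, 54 completers give 84%, still short of 90%.

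**Recruitment target**

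To retain 76 completers after 10% loss would take 76 / 0.9 = 84.4, so 85 recruited. Even on the protocol's own figure, 55 / 0.9 = 61.1, so 62, whereas 60 recruited leaves 54. That last shortfall is a minor matter of one participant.

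**The case against.** The strongest reply is that 72% is the low end of a range. It assumes the full attrition, which the protocol states only as an upper limit, and an exact t-test. With everyone analysed, power is 79%, or 83% by the normal approximation. That is fair, and the result should be given as a range; but every value in it is below 90%.

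It can also be said that the study is described as exploratory. SRMs with 95% confidence intervals will be reported, and the Discussion places estimation above formal testing and disclaims causal superiority between cues. This lessens the harm of a missed effect but does not correct the statement. The Discussion's caution about low power covers only variability and asymmetry, on the ground that the sample size was based on gait speed, so the reader is left to think gait speed is adequately powered. The Statistical analysis section still sets a formal, familywise-controlled test.

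Lastly, a different alpha may have been intended. With a familywise 0.05 (0.0167 per test), 54 completers would give 88% power and all 60 would give 92%, close to the claim. In that case alpha is misstated in two sections, and the text is still wrong as written.

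**Conclusion.** The concern holds. On the protocol's own inputs the requirement is 63 participants (60 by the normal approximation) for one comparison and 76 (72) after Bonferroni, against the printed 54 and 55. At the two-sided 0.0033 fixed for the primary comparisons, power at SRM 0.5 is 72% with the planned 54 completers and 79% with all 60, or 77% and 83% by the normal approximation. The type II error per cue with 54 completers is thus about 28% by paired t, nearly three times the 10% stated.

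The conclusion rests on a paired test of change from baseline and on the SRM of 0.5 that the protocol assumes. It needs no outside figure, and nothing in an unseen analysis plan could make the stated inputs yield the stated numbers.

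**What to change.** Keep the 60 participants and rewrite the Sample size paragraph. State that SRM 0.5 with 90% power needs 63 participants at two-sided 0.01 and 76 at 0.0033 (paired t). State that 60 recruited, with 54 to 60 analysed, gives about 72% to 79% power per cue at SRM 0.5. Add that, with 54 completers, 90% power applies to an SRM of about 0.60 or more. Name the test on which these figures rest. Align the adequate-power claim and the Justification Summary with them, and add gait speed to the power caveat in the Discussion.

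If the team's records show that a familywise alpha of 0.05 was the intended rule, correct alpha to 0.0167 per test in both Sample size and Statistical analysis, and report 88% power with 54 completers. This should be done only on evidence that the intention predates sight of the data, because recruitment was due to close in December 2025; alpha should not be moved to rescue the sample size.

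The cost is the rewording and a less favourable stated power. On the first route neither the conduct nor the analysis changes; on the second, the significance threshold changes as well.

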#### Justification Summary.

A total sample size of 60 PwPD ensures robust and reliable results for both detecting significant changes in gait parameters and assessing the reliability of gait measurements across different auditory cues when compared to the reference standard.

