### Statistical analysis

For the first primary objective, all gait characteristics derived from CuePD and reference will be compared using ICC_2,1_ (absolute agreement), a two-way random-effects model for single measures that evaluate the absolute agreement between raters. The level of agreement will be interpreted as: < 0.5 shows poor agreement, 0.5–0.75 moderate, 0.75–0.9 good and 0.9–1.0 excellent. PCC’s will be calculated to measure the linear correlation between the two sets of results. Correlation coefficients will be interpreted as follows: zero (0), weak (±0.1 to ±0.3), moderate (±0.4 to ±0.6), strong (±0.7 to ±0.9), and excellent/perfect (+1 or −1).

The median, mean, standard deviation (SD), minimum/min, maximum/max, and standardised response mean (SRM) of cadence, stride length, gait speed and CV_stride-time_ will be calculated. These descriptive statistics will provide context for interpreting changes and help to clarify the magnitude and consistency of cueing effects. SRM allows for assessment of responsiveness and comparison of results to other studies. The SRM will be interpreted as: > 0.8 large positive response, 0.5–0.8 moderate responsiveness, and <0.5 low responsiveness where positive values imply an improvement for cadence, gait speed and stride length but negative is an improvement for CV_stride-time_, i.e., reduces variability.

To evaluate the cueing modality adherence, the percentage change in cadence from the baseline walk to each cueing modality will be calculated for each participant. The most effective cueing modality will be identified as the one producing a change closest to 10%.

Model assumptions will be formally checked, where residual normality and normality of gait characteristics within each cue condition will be assessed using the Shapiro-Wilk test, and sphericity with Mauchly’s test. The Greenhouse-Geisser correction will be applied if sphericity is violated.

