### Primary objectives: Validity and evaluating the effects of personalised auditory cues on gait

The impact each personalised auditory cue has on participants’ stride length, gait speed, and${\text{ CV}}_{\text{stride}-\text{time}}$ are a significant exploratory interest. These metrics, in particular${\text{ CV}}_{\text{stride}-\text{time}}$, where a decrease is known to reduce the risk of falling, have indicated variable effects among PwPD in other cueing-related studies, particularly where music cueing is not personalised [9,44,73]. The findings from this study will establish a baseline understanding of their (i) validity (from an app and smartphone worn on the lower back) and (ii) whether personalised cues can consistently reduce stride variability across a broader range of participants.

Observed gait responses will be interpreted in the context of sequence-conditional effects (cue order, exposure, and adaptation over time), and not as definitive evidence of causal superiority of one cueing condition over another. Analyses of gait variability and asymmetry will be interpreted cautiously, as these measures typically exhibit greater dispersion and may be underpowered (as sample size of based on gait speed). Emphasis will be placed on estimating effect sizes and examining consistency of responses across conditions, rather than on formal hypothesis testing.

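### Sixty participants are said to ensure reliable validation and gait-change results, but only gait speed was sized, and the protocol elsewhere says other measures may be underpowered

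*Protocol article*

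**What the plan says.** The Sample size section has one basis: "Sample size calculations were based on detecting changes in gait speed using a within-subject design". Its inputs are "Assuming a standardised response mean (SRM) of 0.5 (moderate effect size) for gait speed" with "a two-sided significance level (α) of 0.01, and 90% power". It reaches 54 for one comparison, about 55 after a Bonferroni adjustment for three comparisons, and 60 after allowing for up to 10% attrition.

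The Justification Summary that follows says the total of 60 "ensures robust and reliable results for both detecting significant changes in gait parameters and assessing the reliability of gait measurements" across the cues, compared with the reference standard. The second half of that assurance is the first primary objective in the Introduction: validation of the app's gait characteristics. The Outcome measures section lists these as means, variability and asymmetry.

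Under Statistical analysis, validation uses ICC(2,1) with absolute agreement, and each ICC receives a verbal label: "The level of agreement will be interpreted as: < 0.5 shows poor agreement, 0.5–0.75 moderate, 0.75–0.9 good and 0.9–1.0 excellent". No expected ICC, minimum ICC or interval width is given.

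In the Discussion, on the primary objectives, the protocol says of gait variability and asymmetry that "these measures typically exhibit greater dispersion and may be underpowered (as sample size of based on gait speed"). It promises cautious interpretation of them.

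**The concern.** A sample size for a mean paired difference says nothing about how precisely an intraclass correlation will be estimated, or about outcomes with a different standardised response. The Justification Summary nevertheless carries the figure of 60 over to both. It also conflicts with the Discussion: the sample cannot ensure robust results for gait parameters in general while some of them may be underpowered for want of a calculation.

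Validation is a co-primary conclusion, and the app's measurements rest on it. If the sentence stands, an agreement label that owes something to sampling error can be defended as coming from a sample chosen to make it reliable. A null finding on a parameter that was never sized can be defended in the same way.

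**Working it through.** **1. The gait-speed calculation, reproduced first.** Inputs from the Sample size section: SRM 0.5, two-sided α 0.01, power 90%, then α = 0.01/3 = 0.0033. The Statistical analysis section repeats the adjusted level: "statistical significance (*p*) will be evaluated at a two-sided α = 0.01/3 = 0.0033".

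Normal approximation: n = ((z₁₋α/₂ + z₀.₉₀)/SRM)².

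- α 0.01: ((2.576 + 1.282)/0.5)² = 59.5, so 60; exact noncentral t gives 63. The protocol states 54.
- α 0.0033: ((2.935 + 1.282)/0.5)² = 71.1, so 72; exact noncentral t gives 76. The protocol states about 55.

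Neither stated figure reproduces. Attrition of 10% from 60 leaves 60 × 0.9 = 54.

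Power of the paired t-test at SRM 0.5 and two-sided α 0.0033, with noncentrality 0.5√n:

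| n | noncentrality | critical t | power |
|---|---|---|---|
| 54 | 3.674 | 3.074 | 72% |
| 55 | 3.708 | 3.071 | 73% |
| 60 | 3.873 | 3.059 | 79% |

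**2. ICC precision.** The documents give no ICC, so the true values below are assumptions. With two systems, one value per person per system and no constant offset between devices, set F = (1 + ICC)/(1 − ICC). The limits are (F/q − 1)/(F/q + 1) and (Fq − 1)/(Fq + 1), where q is the 97.5% point of the F distribution on (n − 1, n − 1) degrees of freedom: 1.723 at n = 54 and 1.674 at n = 60. This is the consistency form, used as an approximation to ICC(2,1).

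Worked example, ICC 0.75 and n = 60: F = 1.75/0.25 = 7. F/q = 4.181 gives 3.181/5.181 = 0.61. Fq = 11.719 gives 10.719/12.719 = 0.84.

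| Assumed ICC | n = 54 | n = 60 | Protocol bands touched |
|---|---|---|---|
| 0.50 | 0.27–0.68 | 0.28–0.67 | poor, moderate |
| 0.60 | 0.40–0.75 | 0.41–0.74 | poor, moderate |
| 0.75 | 0.61–0.85 | 0.61–0.84 | moderate, good |
| 0.80 | 0.68–0.88 | 0.69–0.88 | moderate, good |
| 0.90 | 0.83–0.94 | 0.84–0.94 | good, excellent |

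The total width is 0.24 (n = 54) or 0.23 (n = 60) at ICC 0.75, 0.20 or 0.19 at 0.80, and 0.11 or 0.10 at 0.90.

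A simulation of ICC(2,1) itself (20,000 replicates per setting, normal data, no offset) gives the same ranges for the estimate. With the label read from the point estimate, a true ICC of 0.70 is called good in about 21% of trials at n = 60. A true ICC of 0.60 is called good in about 2%.

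**3. The passages side by side.** Sample size: gait speed only. Justification Summary: gait parameters generally, plus reliability against the reference. Discussion: variability and asymmetry possibly underpowered, because the size rests on gait speed. The first does not support the second, and the third contradicts it. This step needs no assumed figure.

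**The case against.** The best reply is that the Discussion already deals with the weak outcomes: it concedes low power for variability and asymmetry, promises caution and puts effect sizes ahead of formal testing. That stands, and it reduces the practical harm. It does not remove the conflict, because the Justification Summary carries no such qualification.

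Second, the ICC shortfall depends on values the documents do not give. This also stands. A reader might infer that 60 is too few for the validation, but the documents do not support that. From about 0.8 upwards the interval is no wider than 0.20, and an estimate close to a band boundary will straddle it at any sample size. Mislabelling is common only near a boundary, as the 21% against 2% shows.

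Third, a reader might apply α 0.0033 to stride-time variability and conclude that its power is very low. The Statistical analysis section reserves that level for the three primary comparisons and tests stride-to-stride variability at 0.05. There, paired-t power at n = 54 to 60 is 82–86% for an assumed SRM of 0.4 and 58–63% for 0.3.

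Fourth, one might want bands assigned by the lower confidence limit. The protocol sets no such criterion, and the trade-off is debatable: at a true ICC of 0.80 and n = 60, a grade of good or better would fall from about 83% of trials to about 15%.

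Finally, an article may leave interval methods and precision targets to a fuller document. Their absence is not the point here; the affirmative assurance is.

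**Conclusion.** The point holds as a claim the design does not support. Only the gait-speed comparison has a calculation; the ICC validation has none, and the protocol itself doubts the power for variability and asymmetry. The contradiction rests on the text alone.

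The size of the ICC problem rests on assumed true ICCs, normal data and no constant device offset. On those terms, reliable grading is not ensured for characteristics with moderate agreement and is reasonably secure at about 0.8 or higher. Even the outcome that was sized does not have the stated power: at SRM 0.5 and two-sided α 0.0033 it is about 72% with 54 participants and 79% with 60, against 90% stated. Correcting the scope of the sentence without correcting that figure would endorse a calculation that does not reproduce. The correction is worth making because a co-primary conclusion is affected.

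**What to change.** Rewrite the Justification Summary to say three things:

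- Only the gait-speed comparison was formally sized. Its power at SRM 0.5 and two-sided α 0.0033 is about 72% with 54 participants and 79% with 60; correct the Sample size section to match.
- The ICC validation and the other gait outcomes were not formally sized, and variability and asymmetry may be underpowered, as the Discussion says.
- The expected ICC precision at 54 to 60 participants is, for example, about 0.61 to 0.85 around an ICC of 0.75 and 0.83 to 0.94 around 0.90, with these ICCs marked as assumptions.

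In the Statistical analysis section, state that each ICC is reported with a 95% confidence interval beside its agreement label. The bands themselves can stay.

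The cost is a few sentences and one interval per ICC from data already planned, with no extra participants. The price is openness: the article will show less than 90% power for gait speed, and some agreement labels will appear beside intervals that cross a band boundary.

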### Statistical analysis

For the first primary objective, all gait characteristics derived from CuePD and reference will be compared using ICC_2,1_ (absolute agreement), a two-way random-effects model for single measures that evaluate the absolute agreement between raters. The level of agreement will be interpreted as: < 0.5 shows poor agreement, 0.5–0.75 moderate, 0.75–0.9 good and 0.9–1.0 excellent. PCC’s will be calculated to measure the linear correlation between the two sets of results. Correlation coefficients will be interpreted as follows: zero (0), weak (±0.1 to ±0.3), moderate (±0.4 to ±0.6), strong (±0.7 to ±0.9), and excellent/perfect (+1 or −1).

The median, mean, standard deviation (SD), minimum/min, maximum/max, and standardised response mean (SRM) of cadence, stride length, gait speed and CV_stride-time_ will be calculated. These descriptive statistics will provide context for interpreting changes and help to clarify the magnitude and consistency of cueing effects. SRM allows for assessment of responsiveness and comparison of results to other studies. The SRM will be interpreted as: > 0.8 large positive response, 0.5–0.8 moderate responsiveness, and <0.5 low responsiveness where positive values imply an improvement for cadence, gait speed and stride length but negative is an improvement for CV_stride-time_, i.e., reduces variability.

To evaluate the cueing modality adherence, the percentage change in cadence from the baseline walk to each cueing modality will be calculated for each participant. The most effective cueing modality will be identified as the one producing a change closest to 10%.

Model assumptions will be formally checked, where residual normality and normality of gait characteristics within each cue condition will be assessed using the Shapiro-Wilk test, and sphericity with Mauchly’s test. The Greenhouse-Geisser correction will be applied if sphericity is violated.

A two-way mixed ANOVA will be used to assesses the effects of cueing modality and walk order on outcomes, i.e., cadence, gait speed, stride length, and CV_stride-time_. Comparable to the referenced PD study, cueing modality will be modelled as a within-subject factor, while walk order as a between-subject factor to account for potential sequence effects. For each outcome, within-participant changes from baseline will be calculated using cue-specific difference scores. To account for differences in scale and statistical distribution among the outcomes, change scores will be computed using Equations (30)-(31):

Percentage change of gait speed and stride length from baseline, calculated as:

$$\%\Delta =\frac{\text{Cue Value}-\text{Baseline Value}}{\text{Baseline Value}}\times \text{1}\text{0}\text{0}$$
(30)

In contrast,${\text{ CV}}_{\text{stride}-\text{time}}$, a dimensionless ratio-based variable that may have a skewed distribution, change will be computed using the natural log-ratio of cue value to baseline:

$$\Delta_{log}=\text{log}\left(\text{Cue Value}+\in \right)-\text{log}\left(\text{Baseline Value}+\in \right)$$
(31)

where 𝜖 is a small constant to avoid the logarithm of zero. This transformation was chosen as ${\text{CV}}_{\text{stride}-\text{time}}$ is a ratio-based measure that can be highly skewed and exhibit unequal variances across conditions. Applying the *log* transformation to change scores helps to normalise the distribution and stabilise the variance, thereby supporting more reliable statistical comparisons of cueing effects on ${\text{CV}}_{\text{stride}-\text{time}}$ in this within-subjects design. Post-hoc comparisons between cueing modalities will be conducted using paired t-tests, with Bonferroni correction applied to account for multiple comparisons. Effect sizes will be reported using Cohen’s d.

If assumptions for normality are not met, a Friedman test will be used to assess within-subject differences across cueing conditions. Post-hoc Wilcoxon signed-rank tests, with Bonferroni correction, will be conducted only if the Friedman test is statistically significant. For between-subject effects (e.g., walk order), where normality assumptions are violated, the Kruskal–Wallis test will be used to assess group-level differences between walk-order groups. Interaction effects between cueing and walk order will be explored non-parametrically by conducting separate Friedman tests within each walk order group. Effect sizes for non-parametric tests will be calculated using the rank-biserial correlation coefficient, $\text{r}=\text{Z}/\sqrt{\text{N}}$, providing a measure of the magnitude of the effects observed.

For the three primary comparisons, we will control the familywise error rate using a Bonferroni adjustment. Given three cueing modalities, statistical significance (*p*) will be evaluated at a two-sided α = 0.01/3 = 0.0033. Effect sizes (i.e., SRM) and 95% confidence intervals will also be reported. Secondary and exploratory analyses (e.g., comparing cueing modalities to one another, examining washout effects, assessing stride-to-stride variability) will not be subject to multiplicity correction. For these analyses, a two-sided *p*-value of 0.05 will be considered statistically significant across all parametric and nonparametric tests.

To assess whether the first cue produced short-term residual effects, we will calculate changes in gait outcomes from baseline to each cued walk and from each cued walk to its subsequent washout walk (WO1 and WO2). For each cue exposure, a carryover score will be calculated as the difference between the change induced by the cue and the change observed during the corresponding washout period, reflecting retained cue effects. The approach enables an evaluation of carryover effects after each cued walk separately, thereby capturing any cumulative or progressive retention of cueing effects. Group differences based on initial cue type (i.e., counterbalanced sequence) will be evaluated using one-way ANOVA or the Kruskal–Wallis test, depending on normality assumptions [74–80].

To evaluate the relationship between musical sophistication and response to cueing, two sets of analyses will be conducted using Gold-MSI subscale scores. Assumption checks, including the Shapiro-Wilk test and Q-Q plot inspections, will be used to assess the distribution of change scores prior to both analyses. First, the association between Gold-MSI scores and cue adherence (defined as the absolute deviation from a + 10% target increase in cadence) will be assessed using Spearman’s rank correlation coefficient, with Bonferroni correction for multiple comparisons across subscales. Second, associations between Gold-MSI scores and gait outcome improvements (percentage change in gait speed and stride length, and log-ratio change in ${\text{CV}}_{\text{stride}-\text{time}}$) will also be tested using Spearman’s correlation, with Bonferroni correction.

